### Rationale

The ECG is often referred to as the screening test for STEMI. This is because 30-50% of patients with STEMI on ECG will not have an occlusive coronary artery thrombus when evaluated with coronary artery angiography, the criterion (gold) standard diagnostic test. Despite this limitation, the risk-benefit balance of early treatment verses further testing weighs in favor of early treatment. As a result, treatment is initiated based on the *reference diagnostic testing standard*, an ECG demonstrating STEMI. In the context of ED operations and patient flow, the trigger criteria is the

true screening test. Patients, who do not receive an early ECG from registration or triage, go on to receive typical ED care. This provides an opportunity to identify cases missed by the index test, making typical ED care an *alternative reference standard* for trigger negative patients.

We have looked at the STEMI screening performance at Vanderbilt University (Table S1). In doing so we considered a patient meeting trigger criteria, which prompts the ED registration or triage staff to initiate an early ECG, as a positive *index test*, and an ECG indicating STEMI as a positive *reference test*. We found that the screening process has high sensitivity and negative predictive value with poor positive predictive value and limited specificity. The likelihood ratio of positive test is 5.2 (probability of a person with a STEMI ECG screening positive via screening trigger criteria), and that of a negative test is 0.025 (probability of a person with a STEMI ECG not being identified with screening trigger criteria). This study seeks to understand these local results in the context of broader clinical practice and variability of trigger criteria between institutions.

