#### **Data Collection**

A site-PI from each ED will be responsible for extracting aggregate figures included in the study survey (Appendix I) using data from their EMR reporting functions and their hospital STEMI case review committee. To reduce misclassification bias, STEMI is defined using ICD-9 codes previously validated in the literature (410.01, 410.11, 410.21, 410.31, 410.41, 410.51, 410.61, 410.81, 410.91). The EMR will provide aggregated numbers on ED care events (number of patients seen, number of patients receiving an early ECG as a result of triggering the screening criteria, etc.), while the hospital STEMI committee report will provide verifying counts for all ED STEMI cases, whether the early ECG demonstrated STEMI, and missed ED STEMI cases. For any discrepancies between the EMR and STEMI committee reports, the site PI will review the associated patient charts and make a clinical decision on whether the case was Trigger positive or negative, and STEMI positive or negative. The survey is included as appendix I, and will be sent to the site-PIs via email using REDCap. REDCap will also serve as a secure study data repository. The questionnaire has been reviewed by a biostatistician for completeness and to ensure it appropriately supports the planned analysis. (see attached)

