## PERFORMANCE OF STEMI SCREENING TRIGGER CRITERIA

Online form available at: <https://redcap.vanderbilt.edu/surveys/?s=ET3WK99HDM>

---

The electrocardiogram (ECG) is often described as a screening test for ST-elevation myocardial infarction (STEMI), with coronary angiography as the criterion standard diagnostic test. However, in the emergency department (ED), treatment is initiated based on the presence of STEMI on ECG. In addition, timely diagnosis should be made within 10 minutes, well before a patient is seen by a physician and during the processes of registration and triage. As a result, in the context of ED patient care processes and flow, the ECG is the **diagnostic test** and the clinical criteria used to screen arriving ED patients for STEMI in during registration and triage (ECG trigger criteria) is the true **screening test**.

This study seeks to quantify the screening performance of the early ECG trigger criteria used to screen for STEMI across 7 geographically diverse EDs. The screening population includes all ED patients  $\geq 18$  years of age seen in the ED from January 1, 2014 at 12:00am to December 31, 2014 at 11:59am. It assumes that all ECGs done within the first 15 minutes of an ED visit are to screen for STEMI. The **STEMI screening criteria** is the index test. Triggering an early ECG is a positive index test. An **early ECG** (performed  $\leq 15$  minutes after patient arrival) is the reference diagnostic test standard. An ECG demonstrating STEMI is a positive reference test. Patients, who do not receive an early ECG from registration or triage, go on to receive typical ED care. This provides an opportunity to identify cases missed by the index test, making typical ED care an alternative reference standard for trigger negative patients.

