8) What was the total number of 2014 STEMI cases that came through the ED? Include all patients,  $\geq 18$  years of age, who were registered as ED patients? This is either all ED patients with an ED admission or hospital discharge diagnosis of STEMI (via an electronic medical record query for diagnosis “STEMI” or ICD9 codes 410.01, 410.11, 410.21, 410.31, 410.41, 410.51, 410.61, 410.81, 410.91). Confirm this number with your hospital STEMI Case Review Committee. If there is a discrepancy, review the individual patient charts. Based on Vanderbilt data, the incidence of STEMI reported in the literature, and all participant ED patient volumes, there should be no more than 5 cases that require review.

<<Free text response>>

9) What was the total number of 2014 STEMI cases that came through the ED that did not get an early ECG (ECG  $\leq 15$  minutes of arrival)? These are the missed screening cases. This can be obtained as an adjudicated case count from your hospital STEMI committee. Many STEMI quality improvement committees will document time-to-ECG permitting an assessment of those missed by screening. These should not include patients whose were screened, but had STEMI-negative early ECGs.

<<Free text response>>

10) What was the total number of 2014 ED patients who had both an ECG performed and a serum troponin ordered and resulted. This is an estimate of the underlying “chest pain patient” burden.

<<Free text response>>

|                                                                                                                                                                                                                                                                      | Greeter               | Check-in Kiosk        | Registration Clerk    | Triage RN             | Midlevel Provider     | Physician             | Other                 |
|----------------------------------------------------------------------------------------------------------------------------------------------------------------------------------------------------------------------------------------------------------------------|-----------------------|-----------------------|-----------------------|-----------------------|-----------------------|-----------------------|-----------------------|

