|------------------------------------------------------------------------------------------------------------------------------|---------------|-----------------------------------------|--------------------------------------------|-----------------|
|                                                                                                                              |               | STEMI                                   |                                            |                 |
|                                                                                                                              |               | (+)
null false                       | (-)
null true                           |                 |
| Test
(Screening
Criteria)                                                                                              | Screen
(+) | 60
true positive                     | 13,092
false positive
(Type I Error) | 13,152          |
|                                                                                                                              | Screen
(-) | 15
false negative
(Type II Error) | 55,454
true negative                    | 55,469          |
|                                                                                                                              |               | 75                                      | 68,546                                     | 68,621          |
|                                                                                                                              |               | Sensitivity (1-β)
80%                | Specificity
81%                         | Accuracy
81% |

**Table S2:** 2x2 Contingency Table Data (Question numbers included below)

|                                          |             | Disease
ECG = Reference Test |           |       |
|------------------------------------------|-------------|---------------------------------|-----------|-------|
|                                          |             | STEMI (+)                       | STEMI (-) |       |
| Test
Trigger Criteria
= Index Test | Trigger (+) | #8-#9                           | #7-#8+9   | #7    |
|                                          | Trigger (-) | #9                              | #6-#7-#9  | #6-#7 |

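### The reference test is stated as an ECG showing STEMI, but Table S2 is filled from a diagnosis count whose definition can differ between EDs

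*Protocol*

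**What the plan says.** **Reference test stated as the ECG.** The Rationale treats meeting the trigger criteria as the positive index test "and an ECG indicating STEMI as a positive" reference test. The survey introduction (Performance of STEMI Screening Trigger Criteria) names the ECG done within 15 minutes as the reference and adds: "An ECG demonstrating STEMI is a positive reference test". The Table S2 header reads "ECG = Reference Test". For patients who did not trigger, and only for them, the survey introduction allows a substitute, "making typical ED care an alternative reference standard for trigger negative patients".

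**Cases counted by diagnosis.** The Data Collection section says "STEMI is defined using ICD-9 codes previously validated in the literature". Question 8, which supplies the STEMI-positive column total, asks for the number of STEMI cases and explains: "This is either all ED patients with an ED admission or hospital discharge diagnosis of STEMI". It accepts a query on the word STEMI or on the listed codes, and asks for confirmation by the STEMI committee. Question 9 counts STEMI cases without an early ECG, with the instruction "These should not include patients whose were screened, but had STEMI-negative early ECGs". Questions 16 to 24 use a further basis, the final hospital diagnosis.

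**Cell formulas (Table S2).** True positives are #8-#9, false positives #7-#8+#9, false negatives #9 and true negatives #6-#7-#9.

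**The concern.** The stated reference and the counted reference are different things. Data Collection says that committee reports will show whether the early ECG demonstrated STEMI, yet none of the 25 survey items collects that count. The ECG-based 2x2 table therefore cannot be built from the survey, and because the coordinating centre holds only aggregates, the analysis cannot repair it later.

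The second problem is comparability. The second objective relates likelihood ratios to the content of the trigger criteria, with the ED as the unit of observation and seven EDs in all. If one site counts ED admission diagnoses and another counts discharge diagnoses, the two can differ for reasons unrelated to their criteria. With seven units, such a difference cannot be separated from the effect under study.

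**Working it through.** **1. Reproduce the plan's figure.** Table S1 gives #6 = 68,621, #7 = 13,152, #8 = 75 and #9 = 15. The Table S2 formulas give:

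- true positives 75 - 15 = 60
- false positives 13,152 - 75 + 15 = 13,092
- false negatives 15
- true negatives 68,621 - 13,152 - 15 = 55,454

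Sensitivity is 60/75 = 80.0% and specificity is 55,454/68,546 = 80.9%, both as stated. PPV is 60/13,152 = 0.46%. LR+ = sensitivity/(1 - specificity) = 4.19, and LR- = (1 - sensitivity)/specificity = 0.247. The Rationale states 5.2 and 0.025 for these ratios. That is a separate discrepancy and no evidence on the present point; the recomputed values are used below.

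**2. Where discordant patients land.** Both cases are in the trigger-positive row, where the alternative reference standard does not apply.

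| Patient with an ECG within 15 minutes | By the stated reference | In #8? | In #9? | Cell from Table S2 |
|---|---|---|---|---|
| Early ECG negative, STEMI diagnosed later | negative | yes | no (excluded) | true positive |
| Early ECG shows STEMI, no qualifying diagnosis | positive | no | no | false positive |

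**3. Size.** The documents give no rate for either kind of discordance, so every rate below is an assumption applied to Table S1.

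(a) *Early-ECG-negative cases among the 60.* Suppose 5% or 20% of them (3 or 12) are moved to reference-negative. Sensitivity becomes 57/72 = 79.2% or 48/63 = 76.2%.

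(b) *Diagnosis point, unequal loss.* The same ED switches from the ED admission diagnosis to the discharge diagnosis. A share of the 60 trigger-positive cases loses the diagnosis, and the 15 missed cases keep it.

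| Assumed loss among the 60 | Sensitivity | LR+ | LR- |
|---|---|---|---|
| 0% | 60/75 = 80.0% | 4.19 | 0.247 |
| 10% (6) | 54/69 = 78.3% | 4.10 | 0.269 |
| 30% (18) | 42/57 = 73.7% | 3.85 | 0.325 |
| 50% (30) | 30/45 = 66.7% | 3.48 | 0.412 |

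Specificity stays at about 81%.

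(c) *Diagnosis point, equal loss in both rows.* At 50%, the expected counts are 30 trigger-positive and 7.5 missed cases.

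- Sensitivity is 30/37.5 = 80.0%.
- Specificity is (55,469 - 7.5)/(68,621 - 37.5) = 80.9%.
- LR+ is 4.18 and LR- is 0.247, both practically unchanged.
- The case count halves, and PPV falls from 0.46% to 30/13,152 = 0.23%.

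The likelihood ratios therefore move only when the loss of diagnosis differs by trigger status. PPV and the case count move either way.

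**The case against.** The best defence has four parts.

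- **Question 8 may mean a union of the two diagnoses.** An ECG-positive patient given a STEMI diagnosis in the ED would then be counted even if it was later withdrawn, and the false-positive misfiling would shrink. This is a fair reading. But the wording equally lets a site pick one diagnosis point, the query method is a second choice, and questions 16 to 24 use another basis.
- **The exclusion in question 9 is sensible.** The index test is the trigger, not the ECG reading. A patient who triggered an early ECG and did have STEMI was rightly flagged. This stands as an argument for a diagnosis-based reference, but that is not the reference the protocol states.
- **Committee confirmation and chart review protect the counts.** They help against counting errors, and question 8 expects no more than 5 cases to need review. Review starts only when two counts disagree, however, and the site investigator then decides without a stated common criterion. It does not bring seven sites to one definition.
- **The shift in (a) is small.** A fall to between 79% and 76% lies well inside the 95% Wilson interval for 60/75, which is 69.6% to 87.5%. That is true for one site. It does not answer the comparability problem between sites.

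A reader might also take a size from the Rationale's remark that "30-50% of patients with STEMI on ECG will not have an occlusive coronary artery thrombus". Applied to the 60 true positives, it would give 60/0.7 = 86 to 60/0.5 = 120 ECG-positive patients. That would put 26 to 60 of them in the false-positive cell, and make STEMI counts differ 1.4- to 2.0-fold between sites. The documents do not support this. The figure concerns occlusion at angiography, not absence of a coded or ED diagnosis of STEMI, and question 8 also accepts the ED admission diagnosis.

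**Conclusion.** The contradiction is in the text and does not depend on any assumed rate. The reference is stated as the ECG, the cells are filled from diagnoses, and the survey cannot supply the ECG-based table. Question 8 also leaves the case definition open to differ between sites, in a study whose second objective is a comparison between sites.

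The size cannot be derived from the documents. In the assumed range with loss of diagnosis only among trigger-positive cases, sensitivity at a site like that in Table S1 falls from 80% to between 78% and 67%, and LR- rises from 0.25 to between 0.27 and 0.41. With equal loss in both rows, neither changes materially. It would therefore go too far to say that the likelihood ratios are necessarily biased. They are exposed to a bias that the survey neither prevents nor allows anyone to measure.

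**What to change.** - In question 8, delete the choice of diagnosis point and of query. Use one definition at all sites: hospital discharge diagnosis by the listed ICD-9 codes, confirmed by the STEMI committee.
- Put questions 9 and 16 to 24 on the same basis.
- Relabel the reference standard as that diagnosis in the Rationale, the survey introduction and the Table S2 header, and align the matching wording in Objectives and Outcome Measures and in the Final Analysis Plan.
- Add one item from the committee report: of STEMI cases with an ECG within 15 minutes, the number whose early ECG showed STEMI. Use it for a sensitivity analysis that treats early-ECG-negative cases separately.

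Rebuilding the table on the ECG is less practical. Patients whose early ECG showed STEMI but who never received the diagnosis may not appear in committee reports. Finding them could mean reading some 13,000 early ECGs at the Table S1 site alone.

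The cost is one extra survey field, and a reference standard that is no longer called the ECG. The change has to be made before sites submit their aggregates.

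### Survey questions 8 and 9 do not require STEMI to be present on arrival, so later-onset cases enter both the false-negative and true-positive cells and probably inflate the missed-case rate and LR-

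*Protocol*

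**What the plan says.** Question 8 of the survey asks for the year's STEMI cases among adults "who were registered as ED patients". It defines them by diagnosis: "This is either all ED patients with an ED admission or hospital discharge diagnosis of STEMI". No time of onset is mentioned.

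Question 9 asks: "What was the total number of 2014 STEMI cases that came through the ED that did not get an early ECG". It labels the answer "These are the missed screening cases" and adds one exclusion: "These should not include patients whose were screened, but had STEMI-negative early ECGs".

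Table S2 turns these counts into cells. The false negatives are #9 and the true positives are #8-#9.

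Three checks surround the counts:
- Question 8: "Confirm this number with your hospital STEMI Case Review Committee. If there is a discrepancy, review the individual patient charts".
- Question 9: "This can be obtained as an adjudicated case count from your hospital STEMI committee".
- The Data Collection section: where the medical record and the committee disagree, the site investigator is to "make a clinical decision on whether the case was Trigger positive or negative, and STEMI positive or negative".

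The Rationale and the survey introduction describe the reference standard for patients who do not trigger an early ECG as typical ED care.

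**The concern.** The index test is over within 15 minutes of arrival, while the disease window in question 8 can run to hospital discharge. A patient admitted through the ED for another problem who has a STEMI on day 3 qualifies for #8. So does a patient whose STEMI begins after some hours in the ED. Neither had the condition when the trigger criteria were applied, so no criteria could have detected it. The first example also falls outside the typical-ED-care reference that the protocol sets for trigger-negative patients.

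The missed-case rate is a named study outcome, and LR- is one of the two measures that the second objective relates to the content of the trigger criteria. Both depend on the false-negative cell, which is small (15 in Table S1), so a few misplaced cases move them. Only seven EDs are compared, and question 8 offers two diagnosis routes, so sites may also admit late-onset cases to different degrees.

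**Working it through.** **Inputs.** Table S1 gives TP 60, FP 13,092, FN 15, TN 55,454. The number of late-onset cases and the share with an early ECG are not in the protocol. I assume 2 to 4 of the 75 and let the share run from 0% to 100%.

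**Step 1: reproduce Table S1.**
- Sensitivity = 60/75 = 80.0%; missed rate = 15/75 = 20.0%.
- Specificity = 55,454/68,546 = 80.9%.
- LR- = missed rate/specificity = 0.200/0.809 = 0.247.

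Sensitivity and specificity agree with the printed 80% and 81%. The likelihood ratios in the Rationale (5.2 and 0.025) do not follow from this table. That is a separate matter, and they are not used here.

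**Step 2: where a late-onset case goes.** Let L be the number of late-onset cases and q the share of them that had an early ECG.
- No early ECG: counted in #8 and #9, hence a false negative. There are L(1-q) of these.
- Early ECG done and negative: counted in #8, kept out of #9 by the exclusion in question 9, hence a true positive through #8-#9. There are Lq of these.

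**Step 3: correct the counts.** Taking late-onset cases out of #8 and #9 moves the first group to TN and the second to FP under the Table S2 formulas as they stand.
- Corrected missed rate = (15 - L(1-q))/(75 - L).
- Corrected LR- = corrected missed rate/corrected specificity. Specificity stays at about 0.809.

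| Share with early ECG (q) | L = 2: missed rate, LR- | L = 4: missed rate, LR- |
|---|---|---|
| 0% | 13/73 = 17.8%, 0.220 | 11/71 = 15.5%, 0.192 |
| 19% | 13.38/73 = 18.3%, 0.227 | 11.76/71 = 16.6%, 0.205 |
| 80% | 14.6/73 = 20.0%, 0.247 | 14.2/71 = 20.0%, 0.247 |
| 100% | 15/73 = 20.5%, 0.254 | 15/71 = 21.1%, 0.261 |

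The 19% row uses the early-ECG rate among all patients in Table S1: 13,152/68,621 = 19.2%.

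**Step 4: where the direction changes.** Set (15 - L(1-q))/(75 - L) = 0.20. Then 15 - L(1-q) = 15 - 0.2L, so q = 0.80 for any L. The break-even share equals the observed sensitivity. Below it the present counts overstate the missed rate and LR-; above it they understate both.

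**Step 5: why both cells must be corrected.** Take 5 late-onset cases, 4 with an early ECG and 1 without. Removing all five from the STEMI column gives 56/70 = 80.0%, unchanged. Removing only the one in #9 gives 60/74 = 81.1%. A check confined to #9 can only raise sensitivity.

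**The case against.** The survey has safeguards. Question 8 asks for cases that came through the ED and requires confirmation by the STEMI committee. A ward STEMI found by discharge code but absent from the committee's ED list would be a discrepancy and lead to chart review. Since typical ED care is the reference for trigger-negative patients, the site investigator could then call that case negative. Question 9 may be answered from an adjudicated count.

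This stands in part: some late-onset cases will probably be removed. But no check states an onset rule, charts are opened only when the two counts differ, and adjudication is permitted rather than required. On review the investigator settles trigger status and STEMI status. A day-3 STEMI without an early ECG can properly be recorded as STEMI-positive and trigger-negative, and so stay a miss.

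A reader might also infer that all or nearly all late-onset STEMI is booked as missed, so that the missed rate is certainly inflated. The documents do not support this. The exclusion in question 9 sends patients with a negative early ECG to the true positives, which pulls the other way, and nothing gives the share with an early ECG. A patient whose STEMI develops in the ED may well have had one. Nor do the documents show that the bias grows with the complexity of a hospital's admissions. Question 25 collects the case mix index, but the analysis plan does not say that it will be used.

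**Conclusion.** The gap is real. Followed as written, the survey counts STEMI that began after arrival, as a false negative without an early ECG and as a true positive after a negative one. Both are misclassifications of a test applied at the door.

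Net inflation of the missed-case rate and LR- is probable, not certain. It requires that fewer than about 80% of late-onset cases had an early ECG. Only 19% of all patients in Table S1 had one. Patients who later have a STEMI may exceed that, but I see no reason to expect 80% among patients whose STEMI had not begun. That is a judgement; the protocol has no figure.

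The size is unknown. Under the assumed 2 to 4 cases of 75, the corrected missed rate runs from 15.5% to 21.1% and LR- from 0.192 to 0.261, around present values of 20.0% and 0.247. The change is worth making because the affected cell is small and the outcomes that depend on it are central.

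**What to change.** - Reword questions 8 and 9 to count only STEMI judged present at ED arrival.
- Apply the rule to every #8 case, in both #9 and #8-#9. The Table S2 formulas then need no change.
- Do not make a diagnostic first ECG a required condition. That would drop STEMI that was present on arrival but not visible on the first ECG.
- Cases whose early ECG showed STEMI need no further check. The Data Collection section already has the committee report this result, so onset is judged only in the remaining #8 cases.
- Add counts of the cases excluded, split by whether an early ECG was done.
- State the same rule for the chart review in the Data Collection section.

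**Cost.** A wording change, two extra counts and more chart review than the five cases that question 8 expects. At the protocol's 0.16% incidence, #8 would be about 74 (0.0016 × 46,378) to 248 (0.0016 × 155,000) per ED. That is an upper bound, since cases with STEMI on the early ECG drop out. In Table S1 the review would cover the 15 misses plus those of the 60 whose early ECG was negative, a number the protocol does not give. Onset time will be a judgement in some charts.

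### True positives are a residual of two counts that need not share a case list, so a late or untimed STEMI left out of survey question 9 is scored as captured.

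*Protocol*

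**What the plan says.** Table S2 builds the four cells from survey questions 6 to 9. The Trigger(+)/STEMI(+) cell is #8-#9 and the Trigger(-)/STEMI(+) cell is #9. No question asks for the number of STEMI cases that did receive an early ECG.

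The two inputs have different starting points:

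- Question 8, all ED STEMI cases, may be obtained "via an electronic medical record query for diagnosis “STEMI” or ICD9 codes". The site is then told: "Confirm this number with your hospital STEMI Case Review Committee. If there is a discrepancy, review the individual patient charts".
- Question 9 asks: "What was the total number of 2014 STEMI cases that came through the ED that did not get an early ECG". On the source it says: "This can be obtained as an adjudicated case count from your hospital STEMI committee". It adds that many, not all, committees record time to ECG.

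The Data Collection section supplies the reconciliation. It states that "the hospital STEMI committee report will provide verifying counts for all ED STEMI cases, whether the early ECG demonstrated STEMI, and missed ED STEMI cases". It continues: "For any discrepancies between the EMR and STEMI committee reports, the site PI will review the associated patient charts", and the site PI is to "make a clinical decision on whether the case was Trigger positive or negative, and STEMI positive or negative". The survey's Data Collection Sources line names the medical record or committee counts as alternatives.

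**The concern.** A cell obtained by subtraction absorbs every error in the two counts behind it. If a STEMI case is in #8 and its late ECG is not reflected in #9, the formula places it among the true positives without anyone having seen an early ECG for it. The same happens to a case whose ECG time cannot be established, if the site leaves it out of #9.

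Sensitivity, the missed-case rate and both likelihood ratios depend on this cell, and all are named outcomes. The second objective relates likelihood ratios to criteria content across only seven EDs. Differences between sites in how #9 is assembled would therefore be mixed with differences in screening. The coordinating center receives aggregates only and holds no directly counted figure to set against #8-#9.

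**Working it through.** **Inputs.** From Table S1: #6 = 68,621, #7 = 13,152, #8 = 75, #9 = 15. Formulas from Table S2.

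**Reproducing the plan's figures.**

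- TP = #8 - #9 = 75 - 15 = 60
- FP = #7 - #8 + #9 = 13,152 - 75 + 15 = 13,092
- FN = #9 = 15
- TN = #6 - #7 - #9 = 68,621 - 13,152 - 15 = 55,454
- Sensitivity = 60/75 = 80.0%
- Specificity = 55,454/68,546 = 80.9%
- LR- = 0.200/0.809 = 0.247

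The cells, the 80% and the 81% agree with Table S1. (The Rationale section prints a different LR-, 0.025; that is a separate matter. The figures here use the Table S1 cells.)

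**Effect of an omission.** Let k of the 15 missed cases be left out of #9 but kept in #8. Then FN = 15 - k, TP = 60 + k, FP = 13,092 - k and TN = 55,454 + k. Sensitivity is (60 + k)/75, so each case adds 1/75 = 1.33 percentage points.

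| k | TP | FN | Sensitivity | LR- |
|---|---|---|---|---|
| 0 | 60 | 15 | 80.0% | 0.247 |
| 1 | 61 | 14 | 81.3% | 0.231 |
| 3 | 63 | 12 | 84.0% | 0.198 |
| 5 | 65 | 10 | 86.7% | 0.165 |

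The documents give no value for k. The upper end of 5 is borrowed from question 8, which expects at most five cases to need review and does not say whether that is per site or overall.

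**Pooled scale.** Assume 812 STEMI cases (Sample Size section) and a true sensitivity of 80%, so 0.20 × 812 = 162.4 missed. With 5 omissions in total, sensitivity reads 1 - 157.4/812 = 80.6%. With 5 at each of seven sites (35), it reads 1 - 127.4/812 = 84.3%.

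**Can the reconciliation miss such a case?** Suppose the coded and committee totals agree, but some cases are coded and unlisted while an equal number are listed and uncoded. Let l be the late-ECG cases in the first group and m those in the second. A site that uses the coded count for #8 and the committee count for #9 misstates the true positives on its coded list by l - m. The totals match, so confirming a number shows nothing. The error is upward if l > m, downward if l < m, and zero if they are equal.

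**Untimed cases.** If both sources agree that a case is STEMI and neither gives an ECG time, STEMI status is not in dispute and no review is prompted. Question 9 does not say where to put the case, so the site's choice decides the cell.

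**The case against.** A reader might infer that any coded STEMI the committee did not list is automatically a screening success, and that question 9 has no check at all. The documents do not support either. Such a case is an EMR/committee discrepancy, and the Data Collection section sends it to chart review, which settles Trigger status as well as STEMI status. The same section names missed cases among the counts the committee report verifies. Question 8 is not a bare code count, question 9 is defined over all ED STEMI cases, and the committee count is permitted rather than required.

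A reader might also infer that the bias always runs upward, so that an ED with weaker case review looks like a better screener. That holds for a simple omission from #9. It does not follow where list differences offset, because the sign is that of l - m and the documents give neither.

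Finally, questions 19 to 24 ask for door-to-ECG percentiles separately at or below and above 15 minutes, so a site must already hold ECG times for its STEMI patients. This makes reliance on an untimed committee list less likely. It does not close the gap: those items ask for percentiles rather than counts, cover primarily screened patients, and are not tied to #8 or #9.

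What stands is narrower. Reconciliation is described in terms of a number and of verifying counts, question 9 does not tell the site to add reviewed late cases to the committee's figure, and undeterminable timing has no place in the form.

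**Conclusion.** The point holds as a weakness in how the survey feeds Table S2. True positives are inferred rather than counted, from two figures not required to come from one case list, and any late or untimed case left out of #9 but kept in #8 is scored Trigger(+). On Table S1 that is about 1.3 percentage points of sensitivity per case, or 81.3% to 86.7% instead of 80.0% for 1 to 5 omissions. This range assumes that the omitted cases were truly missed, escaped chart review and were not offset by an opposite error. How many such cases there are, and the net direction with offsetting list errors, cannot be learned from the protocol. The existing chart review should catch the differences that show in the totals. The change is a cheap improvement, not the repair of a demonstrated bias.

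**What to change.** Have each site match its EMR and committee STEMI cases by encounter, resolve differences by the chart review already planned, and report from that single list:

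- (a) ECG within 15 minutes of arrival
- (b) ECG after 15 minutes, or none
- (c) ECG time not determinable

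REDCap should check that a + b + c = #8. In Table S2, replace #8-#9 with (a) and #9 with (b). If untimed cases are not in #7, the STEMI-negative cells become #7 - a and #6 - #7 - b - c, which still sum to #6 - #8. Report sensitivity twice, as (a + c)/#8 with untimed cases all captured and as a/#8 with them all missed; the gap is c/#8.

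The cost is two extra survey fields, a sum check and a local match. At the protocol's 0.16% incidence the match covers about 74 cases at the smallest ED (46,378 × 0.0016) to 248 at the largest (155,000 × 0.0016). Sites already need a split at 15 minutes for questions 19 to 24, and only aggregate counts leave the site. The downside is a few hours of site time and possibly a less favourable sensitivity.
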